**Exclusion criteria**
Current substance dependence ICD-10 (F1x.2) or substance abuse in any period up to 3 months prior to referral (exception: tobacco/nicotine, F17.2)
Head injury with more than 5 minutes of unconsciousness
Any coercive measure
Metal implanted by operation
Pacemaker
Pregnancy (assessed by urine HCG)
Female patients: Unwillingness to use safe contraception (Intra Uterine Device/System or hormonal contraceptives) during the study period including the wash out period.
Severe physical illness
Known QT prolongation or congenital prolongation of the QT interval
Medical history of cardiac arrhythmias, as well as other circumstances that may increase the risk of torsade de pointes and/or sudden death, including symptomatic bradycardia, hypopotassemia or hypomagnesemia
Current treatment with drugs known to prolong QT interval^2^
Allergies to any of the inactive ingredients and film coat components^3^

^1^No prior use of antipsychotic medication longer than an episode of two weeks in the previous year and/or 6 weeks lifetime, and/or antipsychotic treatment within 30 days prior to inclusion (Kahn et al., 2018).

^2^Class 1A antiarrhythmics (e.g., quinidine, procainamide); Class 3 antiarrhythmics (e.g., amiodarone, sotalol); certain antibiotics (e.g., gatifloxacin, moxifloxacin).

^3^Pregelatinized starch, magnesium stearate, microcrystalline cellulose, hypromellose, talc, titanium dioxide, polyethylene glycol, and saccharin sodium.

#### Trial Visits and Examinations

The patients will undergo thorough examinations on three overall domains: 1) clinical ratings and assessments; 2) neurocognitive testing; 3) neuroimaging. The examination program is shown in **Table 2**.

**Table 2 T2:** Examination Program of the Sub-Sero Study.

		PATIENTS (N=40)	
		Clinical	Imaging
**Baseline**	**Week 0**	SCAN interview Cognition Blood, ECG, BMI PANSS, BNSS, CDSSSWN, UKU, BOCS, EHI, CGIPSP, GAF, QLS, CSFQ	PET, [¹¹C]Cimbi-36 MRS sMRI/DTI
**Treatment**			
	**Week 1**	**Pimavanserin** (34 mg/day)PANSS, ECG Blood, weight BNSS, CDSS SWN, UKU, BOCS, PSP	
	**Week 2**	PANSS, ECG Blood, weight BNSS, CDSS SWN, UKU, BOCS, PSP	–
	**Week 4**	PANSS, ECG Blood, weight BNSS, CDSS SWN, UKU, BOCS, PSP	–
	**Week 6**	Cognition Blood, ECG, BMI PANSS, BNSS, CDSSSWN, UKU, BOCS, PSP, GAF, QLS, CGI, CSFQ	MRS sMRI/DTI
**Wash out**	**Week 8**	Blood, ECG PANSS	–

SCAN, Schedules for clinical assessment in neuropsychiatry; PANSS, Positive and negative syndrome scale; BNSS, Brief Negative Symptom Scale; BNSS, Calgary depression scale for schizophrenia; BOCS, The Brief Obsessive Compulsive Scale; SWN, Subjective well-being under neuroleptic treatment scale; UKU (measurement of side-effects), Udvalg for Kliniske Undersøgelser; PSP, Personal and Social Performance Scale; EHI, Edinburgh Handedness Inventory; BMI, Body Mass Index; QLS, Quality of Life Scale; CSFQ, Changes in Sexual Functioning Questionnaire; MRS, Magnetic resonance spectroscopy; sMRI, structural Magnetic Resonance Imaging; DTI, Diffusion Tensor Imaging.

#### Clinical Ratings

Symptom severity will be assessed by the PANSS (Kay et al., 1989). Moreover, negative symptoms will be assessed using the Brief Negative Symptom Scale (BNSS) (Kirkpatrick et al., 2011). Depressive symptoms of will be assessed using the Calgary Depression Scale for Schizophrenia (CDSS) (Addington et al., 1993). Symptoms of obsessive compulsive character will be assessed with The Brief Obsessive Compulsive Scale (BOCS) (Bejerot et al., 2014). The Subjective well-being under neuroleptic treatment scale (SWN) (Naber et al., 2001) will used as measure for self-rated wellbeing during treatment and life quality will be assessed with the Quality of Life Scale (QLS) (Heinrichs et al., 1984). Level of functioning will be assessed by the Personal and Social Performance Scale (PSP) (Morosini et al., 2000). We will use the Changes in Sexual Functioning Questionnaire (CSFQ) (Clayton et al., 1997) to asses sexual functioning and side-effects. Handedness will be assessed with Edinburgh Handedness Inventory (EHI) (Oldfield, 1971).

#### Neuropsychiatric Testing

The Cambridge Neuropsychological Test Automated Battery (CANTAB) (Robbins et al., 1994) will be used to assess multiple cognitive domains: working memory, learning and executive functions; visual, verbal, and episodic memory; attention, information processing, and reaction time; social and emotion recognition, decision making and response control. Premorbid IQ will be tested using the Danish version of the National Adult Reading Test (DART) (Hjorthoj et al., 2013) (adapted from the National Adult Reading Test, NART) (Nelson, 1982), and the current intelligence will be assessed with the WAIS-IV battery (Kreutzer et al., 2011).

### Neuroimaging

#### Positron Emission Tomography (PET)

PET-scans using the radioligand tracer [¹¹C]Cimbi-36 will be conducted at Neurobiology Research Unit at Rigshospitalet in order to estimate the cerebral serotonin 2A receptor binding potential. The serotonin 2AR agonist PET radioligand [¹¹C]Cimbi-36 will be produced for human administration, as previously described (Ettrup et al., 2014). All participants will be scanned at baseline in a high-resolution research tomography (HRRT) PET scanner (CTI/Siemens, Knoxville, TN).

PET will not be repeated after 6 weeks. Instead, the relation between plasma pimavanserin and cerebral serotonin 2AR occupancy will be based on data obtained in 5 healthy volunteers: [¹¹C]Cimbi-36 PET will be performed before intake of a single dose of pimavanserin 34 mg. PET will be repeated twice within the next two days to determine the relation between cerebral serotonin 2AR occupancy and plasma-pimavanserin. By measuring patients' plasma- pimavanserin levels after 6 weeks, when in steady-state, we will use this plasma-pimavanserin/2AR occupancy ratio derived from the healthy controls to index patients' serotonin 2AR occupancy.

In order to compare baseline serotonin 2AR binding potential, patients will be compared with a group of comparable healthy historical controls balanced on age and gender from the CIMBI data-base (Knudsen et al., 2016).

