## Materials and Equipment

### Study Medication

Pimavansin (Nuplazid™) is a selective serotonin 2AR antagonist with the recent indication of treatment of hallucinations and delusions associated with Parkinson's disease psychosis (FDA approval, April 2016).

Pimavanserin acts as an inverse agonist and antagonist at serotonin 2A receptors with high binding affinity (Ki value 0.087 nM) and at serotonin 2C receptors with lower binding affinity (Ki value 0.44 nM). Pimavanserin has low affinity for sigma 1 receptors (Ki value 120 nM) and has no appreciable affinity (Ki value >300 nM) to dopaminergic (including D2), serotonin 2B, muscarinic, histaminergic, or adrenergic receptors, or to calcium channels. The mean plasma half-lives for pimavanserin and the active metabolite (N-desmethylated metabolite) are approximately 57 and 200 h, respectively. This results in stable plasma concentrations with only one tablet a day. The median time to maximum concentration (T_max_) of pimavanserin is 6 h and independent of dose. Absorption is independent of meal ingestion. In human plasma, the distribution pimavanserin is predominantly protein bound (~95%) (Vanover et al., 2007).

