#### Secondary Endpoints

Secondary clinical endpoints include reduction in PANSS positive subscale score compared to baseline by week 2 and 4, respectively. Also, we will explore effects on negative, obsessive symptoms, sexual functioning, as well as the proportion of patients achieving symptomatic remission (Andreasen criteria) at week 6 (Robbins et al., 1994).

Secondary neuropsychiatric endpoints comprise in-depth characterization pre-treatment predictors of symptom reduction. Measurements will comprise cerebral serotonin 2AR binding potential, cognition, thalamic glutamate levels, blood test, and genetic analyses. After 6 weeks, also the degree of 2AR occupancy in patients, as indexed by plasma-pimavanserin, will be determined.

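### Week-6 receptor occupancy is derived from a single-dose plasma/occupancy ratio that cannot be constant; a bounded saturable model should replace it

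*Protocol article*

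**What the plan says.** The protocol article (Neuroimaging, Positron Emission Tomography) plans a baseline scan in patients and none on treatment. The link between plasma level and occupancy "will be based on data obtained in 5 healthy volunteers". A baseline scan is "performed before intake of a single dose of pimavanserin 34 mg", and then "PET will be repeated twice within the next two days to determine the relation between cerebral serotonin 2AR occupancy and plasma-pimavanserin". The step from volunteers to patients is one sentence. It takes patients' "pimavanserin levels after 6 weeks, when in steady-state", and states "we will use this plasma-pimavanserin/2AR occupancy ratio derived from the healthy controls to index" their occupancy.

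Under Secondary Endpoints, "the degree of 2AR occupancy in patients, as indexed by plasma-pimavanserin, will be determined" after 6 weeks. Under Study Medication, "The mean plasma half-lives for pimavanserin and the active metabolite (N-desmethylated metabolite) are approximately 57 and 200 h, respectively", and dosing is one tablet a day. No plasma level, single-dose occupancy, value of the ratio or upper bound is given.

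**The concern.** Occupancy cannot pass 100%, while plasma level has no such limit. Plasma level divided by occupancy therefore rises with concentration, and a value measured after one dose does not carry over to the higher levels of repeated dosing. The calibration also comes from a time when a slowly cleared active metabolite has barely built up, and it is used when that metabolite is close to its plateau.

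At stake is how the week-6 occupancy figure can be read. If the ratio is applied as a constant, the reported occupancy is plasma level in other units. It can take impossible values, and it shows wide differences between patients who may all be near saturation.

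**Working it through.** **Plan's own figures.** There is no occupancy, plasma or ratio figure to reproduce. The one stated figure built on the same half-life, the washout under Rescue Medication, does reproduce: 5 × 57 / 24 = 11.875, given as 11.9 days.

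**Inputs from the article.** Parent half-life 57 h, metabolite half-life 200 h, time to peak 6 h (Study Medication); 34 mg once daily for 6 weeks, i.e. 42 days or 1,008 h (Treatment Regimen); 5 volunteers with 2 post-dose scans each within two days (Positron Emission Tomography).

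**Assumptions.** Linear kinetics; single-exponential decline; a hyperbolic curve with maximum 100% as comparator; single-dose occupancy of 25% to 80%, because the article gives none.

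**Step 1, parent accumulation.** R = 1 / (1 − 2^(−24/57)) = 3.95. Day 42 is 1,008 / 57 = 17.7 half-lives, so steady state is complete.

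**Step 2, when a constant ratio passes 100%.** Projected occupancy is single-dose occupancy × 3.95 at matched times after dose, so the threshold is 100 / 3.95 = 25.3%. Sampling times move it:
- scan at 6 h, patient sample at 24 h: the fold is 3.95 × 2^(−18/57) = 3.17, threshold 31.5%;
- scan at 48 h, patient sample at 6 h: the fold is 3.95 × 2^(42/57) = 6.58, threshold 15.2%.

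**Step 3, constant ratio against saturable curve.** With occ = C / (C + EC50), let x = occ / (1 − occ) = C / EC50. The steady-state value is 3.95x / (1 + 3.95x).

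| Single-dose occupancy (assumed) | Constant ratio | Saturable curve |
|---|---|---|
| 25% | 98.8% | 56.8% |
| 40% | 158% | 72% |
| 60% | 237% | 86% |
| 80% | 316% | 94% |

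**Step 4, spread between patients.** At 94.0%, x is 4 × 3.95 = 15.8. A patient with twice that plasma level has 31.6 / 32.6 = 96.9%. A constant ratio would report double the occupancy.

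**Step 5, the ratio within the volunteers.** If occupancy is 80% at 6 h (x = 4), then at 48 h x = 4 × 2^(−42/57) = 2.40 and occupancy is 2.40 / 3.40 = 70.6%. Occupancy per unit of plasma changes by (0.706 / 2.40) / (0.80 / 4) = 1.47. The two scans in one person would thus give different ratios.

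**Step 6, metabolite.** Treated as a single 200 h component, accumulation by day 42 is (1 − 2^(−1008/200)) / (1 − 2^(−24/200)) = 12.1. Against 3.95 for parent, the balance shifts by about 12.1 / 3.95 = 3.1 between calibration and use. The article gives neither the metabolite's 2A affinity nor its level, so this cannot be turned into an error in occupancy.

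**The case against.** The strongest reply is that *ratio* is loose wording. The same section twice speaks of the *relation* between plasma level and occupancy. Two post-dose scans at falling plasma levels suit the fitting of a curve, and a condensed article may leave the equation to the full protocol. This stands in part: nothing says that the ratio is constant. A reader might infer that the plan is bound to produce impossible values. The article does not support that, because it needs both a literal constant and a single-dose occupancy above the threshold, and the second is not given. Even so, *ratio* is the term in the only sentence that says how patients' values are obtained. A stated method that misleads if followed is more than an omitted detail.

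A reader might also infer from twelvefold metabolite accumulation that the index is biased to a similar degree. The documents do not support that either, because accumulation of a compound of unstated 2A affinity is not an occupancy effect.

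It is also true that a saturable curve fitted to the same scans still extrapolates to about fourfold higher levels, and that scans within two days of one dose say little about a metabolite coefficient. Both points stand and limit the fix.

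Finally, the listed neurobiological hypothesis concerns binding potential at baseline, which is measured directly by PET. Week-6 occupancy appears in no listed hypothesis. That limits the reach of the point but does not remove it, since the degree of occupancy is still a named secondary measure.

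**Conclusion.** The point holds for the absolute degree of occupancy at week 6. A single-dose ratio is the wrong function for a saturable quantity at parent levels about 3.95 times higher. If it is applied as a constant, single-dose occupancies of 40% to 80% project to 158% to 316%, where a saturable curve gives 72% to 94%. Values above 100% require single-dose occupancy above about 25% (15% to 32% by sampling time). These sizes rest on linear kinetics, a hyperbolic curve with maximum 100%, and an assumed occupancy range. The missing active metabolite is a real gap of unknown size.

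It would be wrong to conclude that the trial's main results are at risk. Raw plasma level, a constant ratio and any common increasing curve rank patients identically, so rank associations with symptom change are the same under all three. The primary endpoint and the sample size do not use occupancy.

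**What to change.** In the PET section, replace the ratio by a pre-specified model, occupancy = Omax × C / (C + EC50) with Omax at most 100%. Fit it to the ten post-dose scans (5 volunteers × 2), allowing for the pairing of scans within volunteers, and carry its uncertainty into each patient's estimate.

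State two limitations: the extrapolation from single dose to steady state, and the unmodelled active metabolite. A metabolite assay in existing samples is optional, as a descriptive or sensitivity check and not as a fitted second term. If the model cannot be estimated, report the endpoint as plasma pimavanserin exposure and not as occupancy.

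The cost is a change of analysis and wording, with no new scans, visits or patients; the optional assay adds a laboratory cost. The downside is wider uncertainty on occupancy and, if patients are near saturation, little spread between them.

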#### Magnetic Resonance Imaging (MRI)

We will use a Philips Achieva 3.0 T whole-body MRI scanner (Philips Healthcare, Best, The Netherlands) with a 32 channel SENSE Head Coil (Invivo, Orlando, Florida, USA) at the Functional Imaging Unit, Rigshospitalet-Glostrup. The MRI scans will be used for co-registration of PET imaging. In addition, T1- and T2 weighted structural images, diffusion tensor imaging (DTI), and spectroscopy (MRS) sequences will be performed, in order to explore cortical and subcortical brain structures, the integrity of white matter tracts and thalamic glutamate levels before and after treatment.

### Intervention

#### Treatment Regimen

Patients will be treated in monotherapy with tablet pimavanserin (Nuplazid^®^) 34 mg/day, oral administration for 6 weeks. At the end of study there will be a washout period of two weeks. The washout procedure after 6 weeks will be similar to the procedure for switching to rescue medication (described below). At week 8, the patients will be seen for their last follow-up visit. The pimavanserin tablets will be provided by ACADIA Pharmaceuticals and re-packed and re-labelled by “Region Hovedstadens Apotek” according to Danish legislation and good clinical practice (GCP) regulations. No placebo medication will be administered in this study.

Tolerability to pimavanserin and clinical effect will be monitored closely. Intolerable side-effects or clinical worsening (defined as a 20% increase in PANSS positive subscale score compared to baseline PANSS positive score) will result in switching to rescue medication.

#### Rescue Medication

-As primary rescue medication, we will use a benzodiazepine rather than a conventional antipsychotic compound, due to the risk of QTc prolongation after pimavanserin exposure (pimavanserin T½= 57 h). We will use oxazepam at per needed basis: 15–30 mg up to 3 times daily.

-As secondary rescue medication, we will commence conventional antipsychotic treatment with amisulpride (Solian™). Amisulpride is a selective dopamine D2/3 receptor antagonist (50–800 mg/day) and is a first-line compound to treat schizophrenia spectrum disorders in Denmark. Amisulpride will be initiated 7 to 14 days after the switch to oxazepam. The washout period of pimavanserin is estimated based on the assumption that T½= 57 h, and the recommended washout period for a complete washout is 5–10 × T½ (Nelson, 1982) [T½ pimavanserin = 57 h: (5x57h)/24 = 11.9 days]. For the current study, a complete washout is not essential as long as ECG, i.e. the QTc interval, is normal (< 500 msec). Since amisulpride will only be initiated if ECG is normal, we judge a washout period of 7–14 days enough to balance the patient's need of treatment with respect to cardiac safety on the one hand and minimizing side-effects of prolonged benzodiazepine exposure on the other hand.

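### The washout reasoning covers only the parent drug (57 h, 11.9 days) and leaves out the active metabolite (about 200 h, 41.7 days by the same rule), about a third of which remains when the contraception requirement ends

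*Protocol article*

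**What the plan says.** All references are to the protocol article.

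- **Study Medication** gives two half-lives: "The mean plasma half-lives for pimavanserin and the active metabolite (N-desmethylated metabolite) are approximately 57 and 200 h, respectively".
- **Rescue Medication** uses only the first: "The washout period of pimavanserin is estimated based on the assumption that T½= 57 h". It states the rule that "the recommended washout period for a complete washout is 5–10 × T½" and works it out at the lower end as "5x57h)/24 = 11.9 days". The metabolite is not mentioned there.
- **Rescue Medication** then explains why a shorter interval is accepted before amisulpride: "a complete washout is not essential as long as ECG, i.e. the QTc interval, is normal" (QTc below 500 msec), and "we judge a washout period of 7–14 days enough to balance the patient's need of treatment". Amisulpride starts only if the ECG is normal.
- **Treatment Regimen** sets the end-of-study period: "At the end of study there will be a washout period of two weeks", and "At week 8, the patients will be seen for their last follow-up visit".
- **Table 1** excludes women who are unwilling to use safe contraception throughout the study, and counts the washout as part of that time.

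**The concern.** The protocol describes two active species but applies its washout rule to the shorter-lived one alone. Someone who reads only Rescue Medication would take it that the two-week washout exceeds the minimum for a complete washout (14 days against 11.9). For the active metabolite it falls well short.

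For most of the plan this makes no difference, because the protocol does not rely on complete washout before amisulpride. The contraception criterion is different. It has no measured condition such as an ECG, and it lapses when the washout period ends. The sponsor chose to cover the time after dosing. What is at stake is whether that cover lasts as long as the protocol's own rule would suggest for every active species it names.

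**Working it through.** **Inputs.** Half-lives of 57 h (parent) and 200 h (active metabolite), from Study Medication. Rule of 5 to 10 half-lives, from Rescue Medication. Interval of 7 to 14 days before amisulpride, from Rescue Medication. Six weeks of dosing and a two-week washout to week 8, from Treatment Regimen.

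**Step 1: the plan's own figure.** Washout in days = k × T½ / 24.

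- Parent, k = 5: 5 × 57 / 24 = 11.875, or 11.9 days. This reproduces the stated value.
- Parent, k = 10: 10 × 57 / 24 = 23.75 days.

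**Step 2: the same rule for the metabolite.**

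- k = 5: 5 × 200 / 24 = 41.67, or 41.7 days.
- k = 10: 10 × 200 / 24 = 83.3 days.
- Ratio to the parent: 200 / 57 = 3.5.

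**Step 3: is the metabolite fully present when washout starts?** After 42 days of dosing the simple accumulation fraction is 1 − 0.5^(42 × 24 / 200) = 0.97. Taking steady state as the starting point is therefore reasonable for patients who complete six weeks.

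**Step 4: fraction remaining, in two ways.**

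- Simple decay: 0.5^(24d / T½), with d in days.
- With continued formation from the parent (an assumption: first-order, starting from steady state), where kp = ln 2 / 57, km = ln 2 / 200 and t is in hours: M(t)/M(0) = e^(−km·t) + [km / (km − kp)] × [e^(−kp·t) − e^(−km·t)]. The factor km / (km − kp) equals 57 / (57 − 200) = −0.399.

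At day 14 (t = 336 h), simple decay gives 0.017 for the parent and 0.312 for the metabolite. With formation the metabolite figure is 0.312 + (−0.399) × (0.017 − 0.312) = 0.43.

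| Days after last dose | Parent | Metabolite, simple decay | Metabolite, with formation |
|---|---|---|---|
| 7 | 13% | 56% | 73% |
| 11.9 | 3.1% | 37% | 51% |
| 14 (week 8) | 1.7% | 31% | 43% |
| 42 (week 12) | under 0.1% | 3.0% | 4.3% |

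Day 14 is 14 × 24 / 57 = 5.9 parent half-lives but only 14 × 24 / 200 = 1.7 metabolite half-lives.

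**Step 5: what extending contraception would mean.** For completers, 42 days after the week-6 dose is week 6 + 42/7 = week 12. That is 42 − 14 = 28 days beyond the present end.

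**The case against.** The strongest reply is that nothing stated is false. Rescue Medication names its assumption, labels the result as that of pimavanserin and agrees with Study Medication on 57 h. The 11.9-day figure also governs nothing directly: the interval used is 7 to 14 days, complete washout is expressly not required, and the ECG registers any QTc effect whichever species causes it. All of this stands. A reader might infer that amisulpride is started too early, or that there is an unrecognised cardiac risk. The documents do not support that.

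The second reply is that the half-life rule appears only in the discussion of switching to amisulpride, and that no text says contraception must last until washout is pharmacokinetically complete. Contraception ends with a two-week calendar period, not at 11.9 days, and that end may simply have been set to match the last visit. This also stands. It means that the link between the half-life rule and contraception is an extension of the protocol's reasoning, not a contradiction within it. A reader might go further and infer a reproductive hazard. The documents give no reproductive-risk data and no potency or exposure for the metabolite, so the remaining fraction has no stated clinical meaning.

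The third reply is that a journal article leaves pharmacokinetic detail to the full protocol. That carries less weight here, because the article itself gives both half-lives, states the rule, carries out the calculation and fixes when contraception ends.

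Finally, 42 days uses only the lower end of a 5-to-10 range, and with continued formation 4.3% remains rather than 3.0%. Both remarks are correct, which is why the change should be worded as a minimum.

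**Conclusion.** The point holds as a minor one. The washout reasoning is correct for the parent drug but incomplete for an active species that the protocol describes: 41.7 days at the lower end of its own rule (83.3 at the upper) against the 11.9 stated. When contraception ends at week 8, about 31% of the metabolite remains by simple decay, or about 43% with first-order formation. These fractions rest on first-order kinetics, the approximate mean half-lives in the article and steady state at the last dose. Patients who stop early may not have reached steady state.

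The 7-to-14-day interval, the two-week visit schedule and the ECG condition need no change. The primary endpoint is measured at week 6, before washout begins, so it is not affected. The case for longer contraception is one of consistency and precaution, not of demonstrated harm.

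**What to change.** Keep the interval before amisulpride, the two-week washout and the ECG condition. Make two text changes.

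1. **Table 1, contraception criterion:** replace the reference to the washout period with *until at least 42 days after the last dose of pimavanserin*. This is the lower end of the protocol's own rule applied to the metabolite. It also gives one fixed minimum for women switched early, for whom Rescue Medication names a washout of 7 to 14 days rather than a single length.
2. **Rescue Medication:** add *At five half-lives a complete washout takes 11.9 days for pimavanserin and 41.7 days for its active metabolite (T½ about 200 h); the 7–14 day and two-week washouts are therefore incomplete for the metabolite.*

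The cost is one sentence, one changed criterion and about 28 more days of contraception for women who complete treatment. Those days fall after the last visit, so no visit would check them; the requirement would rest on the consent text and a reminder at week 8. No dose, visit, sample size or analysis changes.
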